#### Mental health outcomes

The change in mental and behavioural problems from baseline to post-assessment is measured using the German version of the Strengths and Difficulties Questionnaire (SDQ). It contains five subscales (hyperactivity, emotional symptoms, conduct problems, peer problems and prosocial scale) with five items for each dimension. In order to increase the comprehensibility and applicability for primary school children, the SDQ items have been revised, and each item has been visualised with a picture. The pupil survey is administered using an innovative tablet computer-based procedure and was pre-tested in June 2021 with 908 pupils in 10 primary schools and 43 classes in North Rhine-Westphalia.

#### Direct outcomes

Direct outcomes at the pupil level are emotion-related knowledge and social-emotional skills. Social-emotional skills were operationalised with a random selection of 14 items from the German FEESS questionnaire. The instrument consists of seven subscales, each assessed by two items (social integration, classroom climate, self-concept, attitude to school, willingness to make an effort, enjoyment of learning, feeling of acceptance). In addition, teachers’ diagnostic ability to identify conflicts and problems among pupils is measured by four items.

#### Classroom and organisational outcomes

At the classroom level, classroom disruption, e.g. due to disturbing noises, insufficient preparation by pupils or constant need for reminders, is operationalised with seven items. In addition, bullying and classroom climate (e.g. conflicts among pupils, good relationships in class) are measured with six and four items, respectively. At the organisational level, the extent to which health promotion is embedded in the school mission is assessed with eight items, while organisational commitment is operationalised with a five-item scale.

#### Educational outcomes

In terms of pupils’ educational outcomes, we assess teachers’ and parents’ reports of pupils’ academic achievement in mathematics, reading and spelling, as well as their learning behaviour, which could be rated on a 5-point scale (very good to poor).

#### Implementation

In order to assess the quality of implementation of the intervention, each MindMatters lesson or exercise delivered is documented. The documentation includes information on dose (i.e. number of exercises delivered), variation used, fidelity, deviations and preparedness. As a growing body of research suggests that school mental health interventions that expose the whole class to the same content may also have adverse effects [42, 43], teachers are asked to provide open feedback on each lesson. In this way, unintended events (e.g. harmful effects) or deviations are assessed in a non-systematic approach.

In addition to the activities implemented at the curriculum level, teachers from intervention schools are asked to document their school development activities to maintain and promote mental health as defined in the SchoolMatters intervention module (degree of engagement with the SchoolMatters materials, establishment of a school development team, conducting a needs assessment, creating a project plan and a plan for crisis situations, publicity, raising awareness of the intervention within and outside the school) and to assess satisfaction with support and other feedback.

#### Covariates, mediators and moderators

For both intervention and control schools, it will be recorded whether other mental health interventions were implemented during the study period. Furthermore, both groups will provide information on health promotion activities, school development, readiness to change and health-promoting leadership. Sociodemographic characteristics (sex, age), socioeconomic status and migration background of participants will also be recorded.

#### Data collection, management and statistical analysis

IFT Nord is responsible for the coordination and monitoring of the study. Two study centres (IFT-Nord, Fulda University of Applied Sciences) are responsible for the collection, processing and use of the data. In both study centres, all data will be collected using the same procedures, standards and elaborated instruments of proven psychometric quality. Three different sources of data are used: (1) online survey data from school principals, teachers and parents; (2) pupil survey data collected at classroom level via tablet computers; and (3) paper–pencil questionnaire data from principals, teachers and parents. All data will be stored on a secure IT infrastructure. Data from paper-based questionnaires are stored in a lockable cabinet and are only removed temporarily for data entry. A data safety concept is in place that has been reviewed and monitored by the Ministries of Education of the participating study regions. Data entry is carried out by trained scientific staff and is randomly checked by a second independent researcher. Once collected and entered, all data will be checked for plausibility, consistency and completeness. Data transfer between the two study centres is ensured via a secure connection (e.g. virtual private network (VPN)). The status of the trial will be documented in regular progress reports and by the Federal Ministry of Education and Research. To ensure quality, regular site visits will be organised at the study centres.

Statistical analyses will be performed using the latest version of STATA (Stata Corp., College Station, TX, USA). The main analysis will consist of a multilevel regression in which the primary outcomes are predicted at the pupil level using group status (intervention versus control group), controlled for baseline condition. Group status will be included in the model as a fixed effect and a random intercept will be provided for the cluster variables (study region, school, class). Furthermore, all variables with differences between the intervention and control group at baseline will be included in the model. Further mediation analyses will investigate which mediating mechanisms can be identified. It is assumed that the change in mental health outcomes is caused by improvements in proximal (i.e. direct and class/organisational) outcomes. This requires that the group status (i.e. the intervention) is correlated with the proximal outcomes and that the proximal outcomes are significantly related to the distal outcomes. Mediation effects will be examined using the Baron and Kenny partial correlation analysis approach and structural equation models [44, 45]. Moderator analyses will also examine which school-level factors (e.g. size, social gradient) are associated with or influence the impact of MindMatters. Moderator effects are tested using interaction terms in the regression model. The analysis will first be conducted according to the intention-to-treat principle and additionally compared with a per-protocol analysis. Analysis sample 1 includes all those for whom data are available at both measurement points (complete case analysis, as randomised). Analysis sample 2 includes all those reached at baseline (ITT as randomised). Analysis sample 3 includes all those with data available at both measurement points, and schools without intervention are included in the control group. Multiple imputation is used for missing values. To ensure the methodological quality of all analyses, statistical advice is provided by an independent institute.

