**Fig. 1 Fig1:**
[figure not shown]
SPIRIT figure

Primary schools are eligible to participate if (1) they are from one of the three federal states (North Rine-Westphalia, Rhineland-Palatinate, Schleswig–Holstein), (2) they have not implemented the MindMatters intervention in the past and (3) they agree to be assigned to either the intervention or control group. After enrolment, eligible schools will be randomly assigned 1:1 to either the intervention or control group using the Microsoft Excel random number function, with randomisation stratified by subgroups: federal state, school size, social gradient and level of activity in school health promotion. Within the subgroups, each school will be assigned a random number, with the proviso that, for example, schools with large random numbers will be assigned to the intervention group and schools with small random numbers will be assigned to the control group. Randomisation and communication with schools will be carried out by the investigators. Schools will be informed individually by e-mail of the outcome of the group allocation. Data will be collected at baseline and again 18 months after the start of the intervention, including the perspectives of pupils and teachers (both baseline and post-test) as well as parents (post-test only). While the MindMatters intervention is implemented in the intervention schools according to defined criteria, no intervention is implemented in the control schools. The trial flow of the evaluation study is shown in Fig. 2. The trial has been approved by the Ethical Review Board of Fulda University of Applied Sciences (Nr. 3.1.9.2), the Ministries of Education in Rhineland-Palatinate and Schleswig–Holstein, and registered with the German Clinical Trials Register (DRKS00023762).

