### Recruitment and strategies for achieving adequate participant enrolment

As MindMatters is a complex intervention that addresses several levels, a period of 4 months is estimated for the schools to be recruited. Recruitment takes place in a total of three federal states (Rhineland-Palatinate, North Rhine-Westphalia and Schleswig–Holstein), with all primary schools being invited to participate. As a first step, all school principals will be invited to participate in the study by email. After a reminder by post, all schools will be contacted by telephone by the study team. Schools with a positive response will be contacted personally and will be informed about the process of the study. After agreeing to participate, the principal receives a short online questionnaire to assess the school’s general conditions (e.g. current implementation of school health promotion).

At the pupil level, data response is ensured by having trained academic staff collecting the data in the classroom. The success rate depends largely on the number of pupils with parental consent. To increase the response rate of parental consent forms, parents receive a detailed information letter. To increase the response rate among parents and teachers, the survey is offered both online and in paper–pencil form. The return of data is continuously monitored and reported back to schools at regular intervals. The feedback explicitly states that the significance of participating in the study is highly dependent on the level of data response. To encourage retention and completion of follow-up, schools are promised individual feedback on results at the end of the study. In addition, intervention and control schools will receive regular updates on the status of the study and motivational messages (e.g. greeting cards).

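### Three of the four randomisation strata are not prespecified in the main model, and state enters only as a three-level random intercept: a modest, avoidable loss of precision

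*Protocol article*

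**What the plan says.** The Study design section of the protocol article describes 1:1 allocation of schools with "randomisation stratified by subgroups: federal state, school size, social gradient and level of activity in school health promotion". Schools qualify only if "they are from one of the three federal states", so state has three levels.

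The section on data collection, management and statistical analysis sets out the main model. Pupil-level primary outcomes are predicted "using group status (intervention versus control group), controlled for baseline condition". Group is a fixed effect, and "a random intercept will be provided for the cluster variables (study region, school, class"). A covariate rule follows: "all variables with differences between the intervention and control group at baseline will be included in the model". School size and social gradient are named in that section only as examples of moderators. Activity level is not named there as a covariate of the main model.

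Study region is not defined. The same section mentions a data safety concept "reviewed and monitored by the Ministries of Education of the participating study regions". Education ministries belong to the states, so region most likely means federal state. That is an inference.

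**The concern.** Stratification balances the arms on factors thought to matter for the outcome. The balance makes the treatment estimate more precise, but the analysis shows that precision only if the factors are in the model. If they are left out, their variance stays in the school-level error, the standard error is larger than the design warrants, and the test rejects less often than its nominal level.

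The covariate rule does not repair this. Factors balanced by design are among the least likely to show a baseline difference, and when one does, its inclusion is decided by the data and not by the design.

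Power is already in question here. The Discussion reports pilot intraclass correlations of 0.03 to 0.07 against the 0.01 used for planning, and concedes that small effects may be missed. Precision that needs no additional schools is therefore worth having.

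The region term is a separate matter. The three states are a stratification factor, not a sample of regions, and three levels say very little about a variance.

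**Working it through.** **No planned figure changes.** The sample size makes no allowance for strata. Its design-effect step reproduces: (1 + 14 × 0.01) × 2066 = 2355. It supplies two inputs: 2355 / 40 = 58.9 pupils per school at follow-up and 174 / 40 = 4.35 classes per school.

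**1. Design factors against model terms**

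| Factor used to randomise | In the main model? |
|---|---|
| Federal state | Yes, as a random intercept, if study region means state |
| School size | Only if it differs at baseline |
| Social gradient | Only if it differs at baseline |
| Health-promotion activity | Only if it differs at baseline |

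**2. Region variance on 2 degrees of freedom.** The 95% limits of a variance, relative to its estimate, are 2 / χ²(0.975; 2) and 2 / χ²(0.025; 2), that is 0.27 and 39. The component is close to uninformative.

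**3. Does random versus fixed region matter for the treatment test?** Trials of 40 schools in three regions were simulated, balanced within region on three binary factors and analysed on school means. Intraclass correlation was 0.01 or 0.05, and region and the other factors explained assumed shares of the between-school variance. With 4,000 null and 2,000 alternative runs per setting, random and fixed region differed by less than 1 point in type I error and in power in every setting. Two examples at 0.05: with shares of 20% (region) and 40% (others), type I error was 1.7% under both and power 89.6% against 89.5%; with no prognostic strata, power was 82.3% against 81.5%.

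**4. Effect of the three omitted factors, with baseline adjustment as planned.** Assumptions:

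- 40 schools in 3 × 2 × 2 × 2 strata, halved within strata, odd schools by coin flip.
- Variance of a school mean 0.03 + 0.01/4.35 + 0.96/58.9 = 0.0486, with intraclass correlations of 0.03 (school) and 0.01 (class) assumed.
- Effect 0.15 SD; two-sided 5% test (the article does not state sidedness).
- Strata act equally on baseline and outcome; fixed region indicators stand in for the random intercept, as step 3 allows.
- 3,000 runs per cell.

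Both models contain region and the school-mean baseline; the second adds the three factors.

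| Share of school-mean variance due to all strata | Baseline–outcome correlation | Size, without / with | Power, without / with |
|---|---|---|---|
| 20% | 0.5 | 4.5% / 4.9% | 67.8% / 68.9% |
| 20% | 0.7 | 5.5% / 5.3% | 82.9% / 82.6% |
| 40% | 0.5 | 3.7% / 4.5% | 67.5% / 74.4% |
| 40% | 0.7 | 3.6% / 4.6% | 83.1% / 85.0% |

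The simulation error of a 5% rate is √(0.05 × 0.95 / 3000) = 0.4 points, so the size differences at 20% are within noise. The power changes are +1.1, −0.3, +6.9 and +1.9 points.

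**5. The two ends of the range.** Without baseline adjustment, and with region in both models, the gain is about 6 points at 20% and about 16 at 40%. If the strata explain nothing, the simulation in step 3 gives power of 80.8% falling to 77.9% (intraclass correlation 0.01) and 82.3% falling to 79.3% (0.05) when all strata replace the random region term. That is a cost of about 3 points, or about 2 when the comparison is with fixed region.

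**The case against.** Several stronger readings are tempting, and the case against them is sound.

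- *A reader might infer that the model ignores stratification altogether.* It does not. State, if that is the region meant, is in the model, so three of four factors are at issue.
- *A reader might infer that the random region intercept makes the test conservative.* Step 3 shows that it does not. Any conservatism comes from the three omitted factors. Fixed state effects are the more coherent choice for three levels that also define the strata, but little in the treatment test turns on it.
- *A reader might infer a large power loss.* Comparing no strata with all strata, without baseline adjustment, gives 55% against 62% at a 20% share and 55% against 75% at 40%. That is not the planned analysis, which contains region and the baseline value. The loss shrinks to the range in step 4.
- *A reader might infer that stratification rules out baseline differences, so that the covariate rule can never bring a factor in.* In the simulated 24-cell layout about 11.6 cells per trial held an odd school, and in about 27% of trials at least one of the three factors differed between arms by 15 percentage points or more. The rule could then include it. Inclusion would still depend on the data.
- *A reader might infer a validity problem.* The error is on the conservative side: no bias and no excess of false positives.

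It can also be said that a separate analysis plan may settle the covariates. It may, but the article itself states the fixed part, the random part and a covariate rule, and the point concerns that stated model. What remains is that prespecified adjustment for three design factors is missing from it.

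**Conclusion.** The point holds in a limited form. School size, social gradient and activity level were used to randomise but are not prespecified in the main model, and the rule that could admit them tends to pass over balanced factors. With baseline and region in both models, adding them changes power by about 0 to +1 point if all strata explain 20% of the variance between school means, and by about +2 to +7 points at 40%. It costs about 2 to 3 points if they explain nothing. The size of the test without them is somewhat below 5% at the 40% share. These figures rest on the assumed variance shares, baseline–outcome correlations of 0.5 to 0.7, binary coding of three factors and an effect of 0.15 SD. The article gives neither the shares, nor the correlation, nor the coding. The three-level region variance is poorly estimated but has almost no effect on the treatment test. Severity: minor.

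**What to change.** State in the analysis section that the main model includes federal state, school size, social gradient and health-promotion activity, coded as for randomisation, as fixed effects whether or not they differ at baseline. Replace the random intercept for study region with two state indicators, and define study region if the term is kept. Retain random intercepts for school and class.

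This takes one sentence and one line of code. It needs no new data, since the factors were required to randomise. The statistical cost is a few school-level degrees of freedom: if the three other factors are binary, 2 + 1 + 1 + 1 = 5 of the 38 left after intercept and group, two of them for state. If the factors prove unrelated to the outcome, the cost is about 2 to 3 points of power.

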### Sample size calculation

In this study, schools represent the intervention clusters in which classes and pupils are nested. The power analysis relates to the individual pupil level, taking into account the cluster effect by including the intraclass correlation (ICC). There is no ICC estimate for mental disorders in the target age group, but it is estimated to be rather low compared to substance use or risky behaviour and is therefore set at *p* = 0.01 for the power analysis [22]. While the medium effects can be expected at the level of knowledge for primary school pupils (*d* = 0.5), small effects (*d* = 0.1 to 0.3) are assumed at the level of competence due to the short study period. Given the most recent findings on the prevalence, it is expected that the prevalence of mental health problems in the intervention group will be at most four percentage points lower than in the control group at the post-test.

Assuming an alpha level of 5% and a statistical power of 0.80, the estimated sample size is 2066 (with equal allocation to both groups, i.e. 1033 pupils in the intervention group and 1033 in the control group, https://www.sealedenvelope.com/power). Taking into account an intra-class correlation of 0.01 and a number of approximately 15 pupils per class with parental consent and actually present on the day of the survey, the required total sample size increases as follows: (1 + (15 − 1) × 0.01) × 2066 = 2355. Based on previous studies in primary school education, an attrition rate of about 10% is calculated for the pre-post survey at the pupil level across the different measurement points, so that a total sample of 2615 pupils from 174 classes is required for the baseline test. It is planned to implement this with a total of 40 participating primary schools (20 in the intervention group and 20 in the control group).

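### The main model takes its secondary covariates from observed baseline differences between arms, so they depend on chance imbalance rather than prognostic value

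*Protocol article*

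**What the plan says.** The section on data collection, management and statistical analysis describes the main model: "The main analysis will consist of a multilevel regression in which the primary outcomes are predicted at the pupil level using group status", and this is "controlled for baseline condition". Group status is a fixed effect, and study region, school and class have random intercepts. These terms are fixed. The next sentence adds that "all variables with differences between the intervention and control group at baseline will be included in the model". It does not say which variables are candidates, at what level they are compared, or what counts as a difference.

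Other parts of the article show what could enter:

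- Study design (text below Figure 1): "randomisation stratified by subgroups: federal state, school size, social gradient and level of activity in school health promotion". Apart from region, none of these factors is named as a term of the main model. School size and social gradient reappear only as examples of moderators.
- Covariates, mediators and moderators: "Sociodemographic characteristics (sex, age), socioeconomic status and migration background of participants will also be recorded", and "both groups will provide information on health promotion activities, school development, readiness to change and health-promoting leadership". None of these is fixed in the main model.
- Sample size calculation: 40 schools are planned, 20 per arm.

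The aims section presents the trial as confirmatory.

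**The concern.** If randomisation worked, every baseline difference between arms is a chance event. Its size says nothing about whether the variable predicts mental health at 18 months. Selecting on imbalance therefore uses the wrong criterion. It can admit a variable unrelated to the outcome and leave out a useful predictor that happens to be balanced.

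The stratification factors show this most clearly. The design treats them as important and tends to balance them, so the rule would tend to exclude school size, social gradient and activity level.

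Two things are at stake. First, part of the confirmatory model is unknown until the baseline data have been compared by arm, and the undefined word leaves room to settle it later still. Second, precision may be lost compared with adjusting for a few variables chosen in advance. Most candidates are measured at school or class level, where 40 schools carry the information.

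**Working it through.** The article gives no figure for this rule, so there is none to reproduce. The check has three parts.

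**1. What is fixed and what is open**

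| Term | Status in the main model |
|---|---|
| Group status | always in |
| Baseline value of the outcome | always in |
| Study region, school, class | always in (random intercepts) |
| School size, social gradient, activity level | in only if they differ at baseline |
| Sex, age, socioeconomic status, migration background | in only if they differ at baseline |
| Other school and teacher measures in Table 1 | in only if they differ at baseline |

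**2. How often chance alone would bring a variable in**

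Table 1 has 21 rows. Removing the two MindMatters implementation scores leaves 19. Removing the SDQ, already present as baseline condition, leaves 18. The article states no threshold. Assume a 5% test that respects clustering, and independent variables:

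- P(at least one flag) = 1 − 0.95^18 = 0.60
- Expected number of flags = 18 × 0.05 = 0.9

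For shorter candidate lists the probability is 23% (5 variables) or 40% (10). Many of the scales overlap, so independence is doubtful and these values are only a guide.

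**3. Effect on the test**

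The simulation used 40 school-level values (20 v 20), independent standard normal covariates, a true effect of 0.9 standard deviations (unadjusted power about 79 to 80%) and a two-sided 5% test. The rule means adjusting only for covariates with p < 0.05 between arms. Prespecified means adjusting for all covariates. R² is the assumed share of the variance of the school-level values that the covariates explain. There is no baseline-outcome term. Simulation error is about one point.

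Power with five covariates:

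| R² | Rule | Prespecified | Difference |
|---|---|---|---|
| 0 | 79% | 74% | −5 |
| 0.10 | 78% | 77% | −1 |
| 0.16 | 79% | 80% | +1 |
| 0.20 | 80% | 83% | +3 |
| 0.33 | 79% | 87% | +8 |
| 0.40 | 81% | 92% | +11 |

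The rule stays near the unadjusted power throughout, so it captures almost none of the available gain.

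Type I error in runs with three or six covariates and R² from 0.2 to 0.6:

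- Rule with one fixed threshold: mostly 4 to 5%, lowest 3.2% (at R² = 0.6).
- Prespecified: 4.8 to 5.3%.
- Smallest p-value over five readings of a difference (p < 0.05, 0.10 or 0.20; standardised difference above 0.1 or 0.25): 5.5 to 7.6%.

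**Which R² is plausible?** The article does not say, but its ICCs limit it. With 2355/40 ≈ 59 pupils per school, true between-school variance is a share m × ICC / (1 + (m − 1) × ICC) of school-mean variance:

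- ICC 0.01 (sample size section): 0.59/1.58 = 37%
- ICC 0.03 (pilot, Discussion): 1.77/2.74 = 65%
- ICC 0.07 (pilot, Discussion): 4.13/5.06 = 82%

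This treats the pilot ICCs as school-level, which the article does not state. Covariates explaining 40% of true between-school variance would then explain 0.40 × 37% = 15% to 0.40 × 82% = 33% of school-mean variance. That covers the range from no change to a gain of about 8 points, before allowing for the baseline outcome.

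**The case against.** It can be argued that the model is largely fixed: group status, the baseline outcome and three random intercepts are always in, and the baseline outcome is probably the strongest predictor. This stands. A reader might infer that the whole primary model is open or that all prognostic variables can drop out. The article does not support that, because only the secondary covariates depend on the data.

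A reader might also infer that the rule makes the test invalid. With one fixed threshold it does not; the test is slightly conservative. Inflation needs the definition to be chosen after results are seen. The wording allows this, but nothing in the article shows that it is intended.

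The strongest objection concerns power. It would be tempting to report 81% against 92% as the cost of the rule. That is a favourable case: R² is assumed, and the simulated model lacks the baseline outcome, which the real model always contains. What matters is what the covariates explain beyond it. If they explain nothing, prespecified adjustment loses power. A long fixed list would also use more school-level degrees of freedom than the 0.9 variables the rule admits on average.

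Finally, a condensed article may leave candidate lists and thresholds to an analysis plan. That excuses the missing detail but not the criterion: the article states that imbalance decides inclusion, and an analysis plan that followed it would inherit the problem.

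**Conclusion.** The point holds for the secondary covariates. The stated rule selects on chance imbalance, leaves part of a confirmatory model to the data, and tends to omit three of the factors used to stratify the randomisation. It should be replaced.

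The size is modest and uncertain. No inflation of type I error is shown under one fixed threshold; the 5.5 to 7.6% applies only if the most favourable of five readings is picked afterwards. The power difference runs from about −5 to about +11 points as R² goes from 0 to 0.4, with no material change near 0.16. It rests on assumed covariate strengths, five independent covariates and no baseline-outcome term. The 60% chance of at least one flag rests on an assumed 5% threshold and independent candidates. The case for change therefore rests on specification first and on possible precision second.

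**What to change.** Replace the sentence with a short list of covariates that stay in the model whatever the observed balance:

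- the baseline value of the outcome (already in);
- the stratification factors school size, social gradient and activity level, in the form used for randomisation;
- federal state, entered once: as a fixed term in place of the study-region random intercept if the two coincide;
- pupil sex, and at most one class-level socioeconomic measure.

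Justify the list by the design, not by the baseline table. Data collection ran until September 2023 and this protocol version is dated 6 October 2023, so the list should be dated and fixed before any outcome comparison by arm. Use the same list for all analysis samples. Adjustment for observed imbalance can remain as a labelled sensitivity analysis, with its definition of a difference stated.

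The cost is a small text change, including the region term if it coincides with federal state. No new data are needed and the sample size is unchanged. The downside is a few school-level degrees of freedom. If each of the three school factors has two levels (an assumption) and federal state has three, the stratification terms use 3 + 2 = 5, leaving 40 − 2 − 5 = 33 at school level before the socioeconomic measure. If the covariates prove not to be prognostic, a small loss of power follows.
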